### Strategies to improve adherence to interventions {11c}

A note stating that the patient is enrolled in RECIPE will be written in the participant’s electronic medical records, with a specific statement to contact the treating team prior to the administration of any blood component leading up to the procedure, outside of the emergency setting.

### Relevant concomitant care permitted or prohibited during the trial {11d}

Participants who receive the following blood components in the seven days prior to the procedure (aside from what is allocated according to RECIPE protocol) will be excluded from the trial (FFP, platelet transfusion, cryoprecipitate, Prothrombinex®). During and post-procedure, any blood components or additional procedures required are permitted and will be recorded.

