### Criteria for discontinuing or modifying allocated interventions {11b}

All participants can decide to withdraw from the study for any reason and at any time during the study. If it is before the time of intervention, prophylaxis will be guided by standard of care. The investigator can also decide to withdraw a patient from the study if he/she considers it as necessary (e.g. non-respect of at least one of the selection criteria known after inclusion, or for patient safety). When a patient withdraws from the study, all collected data up until the time of withdrawal will be analysed unless the participant requests deletion of their data.

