### Outcomes {12}

The primary efficacy outcome is the difference in the proportion of procedures requiring prophylactic blood component transfusion, defined as the procedures before which any combination of FFP, platelets and/or cryoprecipitate is given to the participant. The primary safety outcome is the difference in procedure-related bleeding complications between the two groups. Bleeding complications will be defined in accordance with the International Society of Thrombosis and Haemostasis guidelines and include clinically significant bleeding with a ≥ 20 g/L drop in haemoglobin or requiring blood transfusion, readmission, or intervention [33].

The secondary outcomes are comparisons in the following between the standard of care and ROTEM-based decision-making arms: amount (in units) of individual prophylactic blood products (FFP, platelets, cryoprecipitate) given; transfusion-related side effects, procedure-related complications other than bleeding (e.g. thromboses, infection, organ damage) assessed at day 0, day 7 and day 28, hospital length of stay (in days), and survival (which will be further delineated into procedure-related or not). Hospital length of stay and survival will be assessed at day 28, which is the end of the trial.

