### Sample size {14}

Previous studies using other global coagulation assays in patients with cirrhosis undergoing invasive procedures have reported a significant (at least 45%) reduction in the need for prophylactic pre-procedural transfusions [28, 29]. Assuming a modest 30% reduction in pre-procedural prophylactic use of blood products, and with a power of 90% and an alpha of 5%, and accounting for possible drop-outs and missing data of 10%, a total of 56 participants or procedures (28 in each arm) will be needed.

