### Plans to promote participant retention and complete follow-up {18b}

The RECIPE study follow-up duration is only 28 days. For participants who are discharged from the hospital before the day 7 or day 28 follow-up assessments, these will be conducted over the telephone to maximise participant retention and follow-up. For participants who deviate from intervention protocols, an attempt will still be made to collect all outcome data.

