## Statistical methods

### Statistical methods for primary and secondary outcomes {20a}

All statistical analyses will be performed using STATA.

The primary efficacy outcome will be an intention-to-treat analysis, comparing the proportion of procedures requiring prophylactic blood component transfusion between the two randomised groups. The primary safety outcome will be a per-protocol analysis comparing the percentage of procedures associated with a procedure-related bleeding complication between the two groups. The secondary outcomes will either be analysed as intention-to-treat analyses (for survival), modified intention-to-treat (comparing specific blood products or transfusion-related side effects) and per protocol analyses (for procedure-related complications other than bleeding and hospital length of stay). The primary outcomes and secondary outcomes comparing proportions or percentages will be compared using chi-squared or Fisher’s exact tests. The secondary outcomes examining continuous variables will be compared using the Mann–Whitney test. A *p*-value less than 0.05 is considered statistically significant in a two-sided test.

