### Methods in analysis to handle protocol non-adherence and any statistical methods to handle missing data {20c}

The methods used to analyse protocol deviations will depend on the stage at which the protocol deviation occurred. Due to the limited data collection points, we do not anticipate missing data.

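### The rule excluding participants for unallocated blood components before the procedure reaches past randomisation and conflicts with the intention-to-treat primary analysis; if it governs, the effect is inflated, mainly in favour of ROTEM

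*Protocol article*

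**What the plan says.** All places are in the protocol article.

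- **Concomitant care {11d}.** Participants who receive FFP, platelets, cryoprecipitate or Prothrombinex "in the seven days prior to the procedure (aside from what is allocated according to RECIPE protocol) will be excluded from the trial".
- **Outcomes {12}.** The primary efficacy outcome is the proportion of procedures requiring prophylactic transfusion, "defined as the procedures before which any combination of FFP, platelets and/or cryoprecipitate is given to the participant". The definition does not ask whether the product was allocated.
- **Statistical methods {20a}.** "The primary efficacy outcome will be an intention-to-treat analysis". The primary safety analysis is per-protocol.
- **Participant timeline {13}.** The qualifying sample is taken within 24 h of the procedure (72 h for stable outpatients), and randomisation follows it.
- **Exclusion criteria.** A separate washout already bars patients given FFP, platelets or cryoprecipitate in the preceding week. Prothrombinex is not listed there.
- **Choice of comparators {6b}.** Standard-of-care triggers are left to sites and proceduralists.
- **Retention {18b}.** "For participants who deviate from intervention protocols, an attempt will still be made to collect all outcome data".
- **Non-adherence {20c}.** "The methods used to analyse protocol deviations will depend on the stage at which the protocol deviation occurred".

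**The concern.** The rule in {11d} can remove a randomised participant because the primary event happened. Such removal would not be balanced between arms. In the standard-of-care arm, product given on local judgement is nearly always allocated product. In the ROTEM arm, product given after a negative algorithm result is unallocated by definition.

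Overrides are foreseeable. Every randomised patient is one whom the site would normally consider transfusing, and the treating team is unblinded ({17a}). The chart note in {11c} is an adherence safeguard, but it makes an exception for emergencies.

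At stake is whether the primary comparison measures the ROTEM strategy as randomised, or only among participants in whom it was followed. With 28 procedures per arm, a handful of participants matters.

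**Working it through.** **1. Does the rule act after randomisation?** Three features say so. It stands under a heading about care during the trial. It exempts allocated product, which exists only once someone has been allocated. A pre-enrolment washout is stated separately. Since randomisation follows a sample taken at most 24 h or 72 h before the procedure, the seven-day window contains the whole interval from randomisation to procedure.

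**2. The plan's own figure.** Inputs from Sample size {14}: a 30% reduction, "with a power of 90% and an alpha of 5" per cent, 10% drop-out, 28 per arm. From {20a}: significance "is considered statistically significant in a two-sided test". The control rate is not stated. I assume 100%, which fits randomising only patients in the transfusion range. With unpooled variance:

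n = (1.960 + 1.282)² × (0 + 0.7 × 0.3) / 0.3² = 24.5, rounded up to 25 per arm; 25 / 0.9 = 27.8, rounded up to 28 per arm, 56 in total.

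The stated size is reproduced, so 100% v 70% is a reasonable base case.

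**3. Direction.** Let n be the ROTEM arm size, k the number algorithm-positive and o the number transfused despite a negative result.

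- Intention-to-treat proportion: (k + o)/n
- After exclusion: k/(n − o)
- Difference: o(n − k − o) / [n(n − o)]

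This is positive whenever there is at least one override and at least one ROTEM participant goes untransfused. Exclusion then always lowers the ROTEM proportion.

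**4. Size.** Let q be the algorithm-positive share and r the override share among algorithm-negatives. Intention-to-treat gives q + (1 − q)r; exclusion gives q / [q + (1 − q)(1 − r)]. The documents give no r, so 5–40% is assumed. Standard of care is taken as 100%. Cells show the risk difference in percentage points, intention-to-treat v after exclusion.

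| q | r = 10% | r = 20% | r = 40% | Inflation over r = 5–40% |
|---|---|---|---|---|
| 70% (design's 30% reduction) | 27.0 v 27.8 | 24.0 v 25.5 | 18.0 v 20.5 | 0.4–2.5 |
| 50% | 45.0 v 47.4 | 40.0 v 44.4 | 30.0 v 37.5 | 1.2–7.5 |
| 30% | 63.0 v 67.7 | 56.0 v 65.1 | 42.0 v 58.3 | 2.4–16.3 |

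The base case does not depend on a 100% control rate. With 90% in standard of care, q = 60% and r = 20%, the differences are 22.0 v 24.8.

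**5. Significance.** Take 28/28 transfused in standard of care, k from 8 to 20 and o from 2 to 6 (13 × 5 = 65 scenarios). Two-sided Fisher tests change from non-significant to significant in 7, all with k of 17–20 and o of 3–6.

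- k = 20, o = 3 (override share 3/8 = 37.5%): 23/28, p = 0.052; after exclusion 20/25, p = 0.019. This is the only one of the seven with an override share of 40% or less.
- k = 20, o = 4 (share 4/8 = 50%): 24/28, p = 0.111; after exclusion 20/24, p = 0.039. Uncorrected chi-squared gives 0.038 and 0.025, so no change. Expected counts near 2 would normally point to Fisher, but {20a} allows either.

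**The case against.** The best counter-argument is that {11d} merely re-anchors the washout to the procedure date, and that its bracket only stops trial product from triggering it. The section does not say that an excluded participant leaves the analysis, and the only statement about the primary analysis set is intention-to-treat. If that statement governs, there is no bias. Section {18b} helps this reading: outcome data on deviators are still sought, so an intention-to-treat analysis stays feasible.

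This stands in part. It makes the inflation conditional. It does not remove the conflict, because the wording and timing of {11d} naturally cover randomised participants, {18b} promises an attempt at collection rather than inclusion, and {20c} settles nothing. The brevity of {20c} is not itself a fault, since an analysis plan may fill it.

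Four stronger readings are tempting but not supported:

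- *Only the ROTEM arm is affected.* Product outside hospital practice would also be unallocated under standard of care, and its removal would bias the other way. It should be rarer, so the imbalance is mainly, not wholly, in favour of ROTEM.
- *An investigator can withdraw a ROTEM patient and revert to standard of care.* Section {11b} does say "The investigator can also decide to withdraw a patient from the study if he/she considers it as necessary", but its sentence on reverting follows the one on the participant's own withdrawal. The section also keeps data collected up to withdrawal, unless deletion is requested.
- *The primary safety comparison is biased by this rule.* That analysis is per-protocol, so deviators could leave it regardless. That overridden patients are those at highest bleeding risk is conjecture.
- *The trial's conclusion would flip.* It does so in 7 of 65 scenarios, nearly all with override shares above 40%.

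**Conclusion.** The conflict is in the text and should be corrected. As written, {11d} allows exclusion after randomisation on the occurrence of the primary event, against the intention-to-treat analysis in {20a}, with no statement of which prevails.

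A reader might infer that the reported effect will be inflated. The documents do not support that as a certainty: overrides must occur, and {11d} must be carried into the analysis set. If both hold, the direction is fixed for ROTEM-arm overrides. The size is modest at the design's own effect, 0.4–2.5 points, and reaches 16.3 points in the most extreme case examined (30% algorithm-positive, 40% overridden). These figures rest on an assumed 100% standard-of-care rate, assumed override rates of 5–40%, and no unallocated product in the standard-of-care arm.

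The Prothrombinex mismatch is a separate, smaller point. Someone who has recently received it can meet the eligibility criteria, be randomised and then fall under {11d}. It is not a primary-outcome product, so the argument above does not extend to it.

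**What to change.** 1. In {11d}, limit the exclusion to products given before randomisation.
2. Reconcile the Prothrombinex entry between {11d} and the exclusion criteria.
3. In {20a}, state that every randomised procedure stays in its assigned arm for the primary efficacy analysis.
4. In {12}, state that any FFP, platelets or cryoprecipitate given between randomisation and the procedure counts as an event, allocated or not.
5. In {20c}, state that such deviations are removed only from the per-protocol sets.

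The cost is wording. The sample size stays at 56, and {18b} already provides for seeking the data. The downside is that the estimated reduction may be slightly less favourable to ROTEM than under exclusion.

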### Provisions for post-trial care {30}

Participants are encouraged to seek assessment and/or treatment from their general practitioner or treating team if they suffer from any medical problems during the trial. They are also encouraged to make their study team aware of any new medical issues, so their relationship with the trial can be evaluated.

### Outcomes {12}

The primary efficacy outcome is the difference in the proportion of procedures requiring prophylactic blood component transfusion, defined as the procedures before which any combination of FFP, platelets and/or cryoprecipitate is given to the participant. The primary safety outcome is the difference in procedure-related bleeding complications between the two groups. Bleeding complications will be defined in accordance with the International Society of Thrombosis and Haemostasis guidelines and include clinically significant bleeding with a ≥ 20 g/L drop in haemoglobin or requiring blood transfusion, readmission, or intervention [33].

The secondary outcomes are comparisons in the following between the standard of care and ROTEM-based decision-making arms: amount (in units) of individual prophylactic blood products (FFP, platelets, cryoprecipitate) given; transfusion-related side effects, procedure-related complications other than bleeding (e.g. thromboses, infection, organ damage) assessed at day 0, day 7 and day 28, hospital length of stay (in days), and survival (which will be further delineated into procedure-related or not). Hospital length of stay and survival will be assessed at day 28, which is the end of the trial.

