#### Standard of care intervention

Participants assigned to the standard of care intervention will receive prophylactic blood components (FFP, platelet transfusion, cryoprecipitate) based on INR and platelet count prior to their procedure. The INR and platelet cut-offs used to determine whether blood product is required, the type and dose, will be based on standard of care at the hospital where the procedure is taking place, and as such may vary between sites and procedures. The required blood products are ordered and administered to the patient immediately prior to the procedure.

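### Prothrombinex bars a participant under the concomitant-care rule but is missing from the exclusion criteria and the primary outcome, so a recipient may be removed after randomisation or, under certain conditions, scored as untransfused

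*Protocol article*

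**What the plan says.** Several sections of the protocol article list products, and the lists differ.

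- **Outcomes {12}.** The primary efficacy outcome is the difference in the proportion of procedures needing prophylaxis, "defined as the procedures before which any combination of FFP, platelets and/or cryoprecipitate is given to the participant". The secondary outcome on units given names the same three products.
- **Exclusion criteria, under Eligibility criteria {10}.** This list decides who is kept out of randomisation. It bars patients given FFP, platelets or cryoprecipitate in the preceding week. Prothrombinex is not on it.
- **Relevant concomitant care {11d}.** Four products are called blood components. Participants who receive one "in the seven days prior to the procedure (aside from what is allocated according to RECIPE protocol" are covered by the rule and "will be excluded from the trial (FFP, platelet transfusion, cryoprecipitate, Prothrombinex".
- **Standard of care intervention.** Participants "will receive prophylactic blood components (FFP, platelet transfusion, cryoprecipitate) based on INR and platelet count prior to their procedure", but the cut-offs and "the type and dose, will be based on standard of care at the hospital where the procedure is taking place".
- **Statistical methods {20a}.** "The primary efficacy outcome will be an intention-to-treat analysis".

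The section on retention {18b} says that outcome data will still be sought from participants who deviate from the intervention. The section on non-adherence {20c} says only that the handling of a deviation depends on the stage at which it occurred.

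**The concern.** The protocol treats Prothrombinex as a blood component in one place and leaves it out of two closed lists elsewhere. Two different problems can follow.

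The first is at entry. A patient given Prothrombinex three days before the procedure meets no listed exclusion criterion on that account, yet falls under the concomitant-care rule. If the rule is applied only after allocation, the trial loses a randomised participant on a fact that could have been known at screening. The same rule can also remove someone for any of the four products received between randomisation and the procedure. That is more serious, because the study investigator and treating team know the allocation, so both the giving of product and the removal could differ by arm.

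The second is in scoring. If Prothrombinex is the only product given before a procedure and the participant is analysed, the procedure counts as one without prophylaxis. In the standard-of-care arm this would dilute the effect; in the ROTEM arm it would look like a saving that did not occur.

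**Working it through.** **1. The lists side by side**

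| Section | FFP | Platelets | Cryoprecipitate | Prothrombinex |
|---|---|---|---|---|
| Exclusion criteria {10} | yes | yes | yes | no |
| Concomitant care {11d} | yes | yes | yes | yes |
| Standard of care intervention | yes | yes | yes | not named; type left to the hospital |
| Primary and units outcomes {12} | yes | yes | yes | no |

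**2. How much of the seven-day window precedes randomisation.** Under Participant timeline {13}, the qualifying blood sample is taken within 24 h of the procedure (72 h for stable outpatients), and randomisation follows it. Seven days are 168 h. At least 168 − 24 = 144 h of the window therefore precede the sample for inpatients, and at least 168 − 72 = 96 h for outpatients. Most prior receipt is thus knowable before allocation. The rest of the window can fall after allocation.

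**3. What can happen to a randomised recipient of Prothrombinex alone**

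- Off-protocol and removed under {11d}: not scored at all, but lost from an intention-to-treat analysis.
- Off-protocol and kept under {20a} and {18b}: scored as no prophylaxis under {12}.
- Given as a site's standard of care: arguably inside the carve-out in {11d} for allocated product, so kept, and scored as no prophylaxis under {12}.

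The first excludes the other two for the same patient.

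**4. The plan's own sample size.** Inputs from Sample size {14}: 30% reduction, 90% power, alpha 5% (two-sided, from {20a}), 10% loss, 28 per arm. The control rate is not stated; 100% is assumed here, so that 30% means 70% on either an absolute or a relative reading.

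n = (1.960 + 1.282)² × [p1(1 − p1) + p2(1 − p2)] / (p1 − p2)² = 10.51 × (0 + 0.21) / 0.09 = 24.5, so 25 per arm. Then 25 / 0.9 = 27.8, so 28 per arm and 56 in total. The stated figure is reproduced. Adding Prothrombinex to a list changes none of these inputs. The 100% is what makes 56 come out: the same formula gives 37 per arm for 95% v 65% and 44 for 90% v 60%.

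**5. Weight of one procedure.** 1/28 = 3.6 points; 3/28 = 10.7 points. With 25 evaluable per arm, 1/25 = 4 points.

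**6. Illustration only.** The protocol gives no rate of Prothrombinex use. Zero to three procedures per arm is an assumption. Power is from the pooled two-proportion formula, 25 evaluable per arm, true rates 100% v 70%:

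z = [(p1 − p2)√n − 1.960 √(2p̄(1 − p̄))] / √[p1(1 − p1) + p2(1 − p2)]

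With none misscored: (0.30 × 5 − 1.960 × 0.505) / 0.458 = 1.11, power 0.87. With one misscored in standard of care, p1 = 24/25 = 0.96: (0.26 × 5 − 1.960 × 0.531) / 0.498 = 0.52, power 0.70.

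| Prothrombinex-only procedures scored as none | Power, standard of care only | Observed difference, ROTEM only | Power, same number in both arms |
|---|---|---|---|
| 0 | 0.87 | 30 points | 0.87 |
| 1 | 0.70 | 34 points | 0.79 |
| 2 | 0.51 | 38 points | 0.73 |
| 3 | 0.34 | 42 points | 0.68 |

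**The case against.** The strongest reply is that the outcome matches the intervention as described. The objectives, the standard-of-care section and the outcomes all name the same three products, and leaving the type to the hospital most naturally means a choice among them. A list of prohibited products may properly be wider than an endpoint list. Off-protocol Prothrombinex leads to exclusion, not to a favourable score. The concomitant-care rule also sets no time at which it is applied, so it can be read with the exclusion criteria and used at screening.

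Much of this stands. A reader might infer that any Prothrombinex use counts as no transfusion, or that every recent recipient is randomised only to be removed. The protocol supports neither. The first needs one of the two conditions set out in the working; the second is one possible sequence, not a stated one. Nor can a false saving be attributed to the ROTEM algorithm, because its figure is not available here. The sizes are also no evidence of frequency: 1/28 is simply the weight of any one procedure.

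What does not stand is that the text already solves the entry problem. The exclusion criteria govern randomisation. The wider rule sits under care during the trial, speaks of participants, excludes from the trial, and has a window that runs to the procedure. Nothing reconciles that removal with an intention-to-treat analysis.

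**Conclusion.** The concern holds in two parts of unequal strength.

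The firm part is the mismatch between the exclusion criteria and the concomitant-care rule. A recent Prothrombinex recipient meets no listed bar to randomisation but is to be excluded from the trial, so may be randomised and then removed. The rule also reaches product received after randomisation, against the planned intention-to-treat analysis.

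The conditional part is the outcome definition. A procedure covered only with Prothrombinex can score as untransfused if it is given as local standard of care, or if an off-protocol recipient is kept in the analysis. Whether either occurs is unknown. Each case would move its arm by 3.6 points out of 28 procedures; the assumed range of zero to three gives 0 to 10.7 points, and zero is quite possible. The power figures rest further on the assumed 100% control rate and 25 evaluable per arm. In a trial of 56 procedures a single classification is not negligible, but the sample size itself is unaffected.

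**What to change.** 1. Reconcile the exclusion criteria with the concomitant-care section, so that prior Prothrombinex is screened for before randomisation.
2. State that participants who receive any listed product after randomisation stay in the intention-to-treat analysis of the primary efficacy outcome, with the receipt recorded as a deviation where it was not allocated.
3. Count Prothrombinex given as pre-procedural prophylaxis as a prophylactic component in the primary and units outcomes. Because recruitment began in February 2021, the alternative is to leave the primary definition alone and report this count as a pre-specified sensitivity analysis.

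None of this alters which product anyone receives. The cost is a few words in three or four sections, one extra data field, and possibly a few more screening failures. It is still a protocol modification, and under the section on amendments {25} it needs approval from the DSMB and from the ethics and research governance committee before use. Prothrombinex given to participants already enrolled would have to be retrieved from the medical records, preferably by someone unaware of allocation.

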### Participant timeline {13}

We aim to investigate 56 interventions in cirrhotic patients with coagulation abnormalities at the study sites. We will recruit patients from both outpatient clinics and inpatient wards who are scheduled for an upcoming invasive procedure, and who would usually be considered for blood components as bleeding prophylaxis prior.

The schedule of enrolment, intervention and assessments is displayed in Fig. 2. All patients meeting eligibility criteria will have a blood sample taken within 24 h of their upcoming planned procedure (72 h for stable outpatients). If platelets and/or INR are within the range that the patient would normally be given FFP or platelet transfusion prior to the procedure as per standard of care (institution-based), ROTEM analysis will be performed, and the patient will proceed to the randomisation phase.

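### Length of stay is rank-tested with no rule for death, so an early in-hospital death can count as a short stay; a death-inclusive comparison in all randomised would avoid this

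*Protocol article*

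**What the plan says.** Outcomes {12} lists among the secondary comparisons "hospital length of stay (in days), and survival (which will be further delineated into procedure-related or not"), and sets the horizon: "Hospital length of stay and survival will be assessed at day 28, which is the end of the trial". It does not say on which day the stay starts.

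Statistical methods for primary and secondary outcomes {20a} fixes the test: "The secondary outcomes examining continuous variables will be compared using the Mann–Whitney test". The same section fixes the analysis set, assigning "per protocol analyses (for procedure-related complications other than bleeding and hospital length of stay"), whereas survival is analysed by intention to treat. The significance rule is also there: "A *p*-value less than 0.05 is considered statistically significant in a two-sided test".

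Section {20c} on non-adherence and missing data says only that missing data are not expected. No section gives a worst rank for death, a restriction to survivors, a competing-risk method or a count of days alive and out of hospital.

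**The concern.** A stay counted in days ends when the patient dies. In a plain rank test a patient who dies in hospital on day 1 therefore gets the same low value as a patient sent home well on day 1. If early deaths are more frequent in one arm, that arm's stays are pulled down and it can appear to do better on this outcome.

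Deaths are plausible here. The Discussion describes advanced liver disease with a high baseline surgical risk, low-risk procedures are limited to 25–30%, and survival is an outcome split by relation to the procedure. The trial aims to show that less prophylaxis can be given while clinical outcomes are maintained. A length-of-stay result that can credit an early death is weak support for that.

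The separate survival analysis does not repair the length-of-stay comparison. It is also done in a different set of patients (intention to treat against per protocol). Section {17a} says the treating team is not blinded, so deviations could differ by arm, and a per-protocol set can then lose the balance that randomisation gave.

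**Working it through.** **The plan's own figure.** The article computes a sample size only for the primary outcome: "Assuming a modest 30% reduction in pre-procedural prophylactic use of blood products, and with a power of 90% and an alpha of 5"%, with 10% for drop-out, giving 56 (28 per arm). The control rate is not stated. Assuming 100% against 70%, with the unpooled two-proportion formula:

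- n = (1.960 + 1.282)² × (0 + 0.7 × 0.3) / 0.30² = 24.5, rounded up to 25 per arm.
- 25 / (1 − 0.10) = 27.8, rounded up to 28 per arm, 56 in total.

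This matches, so 28 per arm is used below. The article gives no figure for length of stay or mortality.

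**Size per death.** With no ties:

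- SD(U) = √(28 × 28 × 57 / 12) = √3724 = 61.0.
- A patient is compared with 28 patients in the other arm, so moving one death from best to worst rank shifts U by at most 28.
- 28 / 61.0 = 0.46 on the z scale for one death; 2 × 0.46 = 0.92 for two.
- From a neutral middle rank the most one death can move is 14 / 61.0 = 0.23.

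The two-sided 5% threshold is 1.96. Ties alter the figure: a death tied with a discharge shifts U by less, and SD(U) is also smaller.

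**Direction and dependence on timing.** These are simulations with 3,000 runs per setting, 28 per arm, and the same lognormal stay in both arms, capped at 28 days. Mortality, day of death and median stay are all assumptions. *Share* is the probability that a patient in the higher-mortality arm has the longer stay, with 0.50 as neutral. The last two columns give the percentage of runs significant in favour of, and against, the higher-mortality arm (nominal 2.5% each).

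| Mortality | Days of death | Median stay | How death enters | Share | In favour | Against |
|---|---|---|---|---|---|---|
| 20% v 5% | 1–3 | 7 | stay ends at death | 0.43 | 13.7% | 0.2% |
| 20% v 5% | 1–3 | 7 | worst rank | 0.58 | 0.1% | 16.2% |
| 10% v 0% | 1–3 | 7 | stay ends at death | 0.45 | 8.3% | 0.6% |
| 20% v 5% | 1–3 | 2 | stay ends at death | 0.47 | 7.0% | 0.7% |
| 20% v 5% | 1–7 | 7 | stay ends at death | 0.45 | 9.5% | 0.2% |
| 20% v 5% | 1–28 | 7 | stay ends at death | 0.49 | 4.0% | 1.5% |
| 20% v 5% | 1–7 | 2 | dying patients stay until death | 0.52 | 1.5% | 4.5% |
| 20% v 5% | 1–28 | 7 | dying patients stay until death | 0.53 | 1.2% | 4.6% |

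In the rows marked *stay ends at death*, death cuts short the stay the patient would otherwise have had. In the last two rows patients who die remain in hospital until they die.

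Early deaths thus push the comparison towards the arm where they occur. Deaths spread over 28 days leave it near neutral (0.48–0.50 across the median stays tried) or, if the dying stay until death, turn it the other way (0.51–0.56). Giving death the worst rank counts it against the higher-mortality arm in every setting (0.55–0.58).

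**The case against.** **The article does not state this ranking.** That is true. It follows from reading a stay in days literally, and an analysis plan not shown here might add a rule for death. What stands is that outcome, horizon, test and set are all fixed in the text, and together they lead to this ranking unless something is added. A stay cut short by death is not missing data, so section {20c} does not cover it.

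**Stronger readings that the article does not support.**

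- A reader might infer that the arm with more deaths will look better. That holds only for early in-hospital deaths. Deaths after discharge do not shorten the stay, and in a trial where "We will recruit patients from both outpatient clinics and inpatient wards" many stays may be so short that a day-1 death merely ties with ordinary discharges.
- A reader might infer that pooling inpatients with outpatients biases the comparison. Under 1:1 randomisation it adds noise, not bias.
- A reader might infer that the stay includes days before randomisation. The start of the stay is not stated, so this cannot be asserted.
- A reader might take 0.46 per death as the expected effect. It is the no-ties maximum, and the number of early deaths among 56 procedures is unknown and could be none.

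**Harm would not be hidden.** Survival is analysed separately by intention to treat, and serious adverse events go to the safety board. This is a fair reason to rate the point low. It does not correct the direction of the length-of-stay test.

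**Replacing a named outcome in a registered, recruiting trial is more than a change of wording.** This objection is accepted. The outcome can be kept and only its between-arm test changed.

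**Conclusion.** The concern holds in a limited form. As fixed, the length-of-stay comparison has no rule for death and, read literally, gives an early in-hospital death the rank of an early discharge, which can favour the arm with more early deaths. The shift is at most 0.46 in z per death with 28 per arm and no ties. It is small, or can reverse, when deaths come late or usual stays are very short. The simulated rates rest on assumed mortality, timing and stay, because the article gives none of these. Using the per-protocol set adds a second, separate weakness. No primary conclusion, sample size or stopping decision depends on this outcome, so the point is a desirable improvement and not a serious fault.

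**What to change.** Keep hospital length of stay as the named secondary outcome. Change its between-arm test to a death-inclusive rank comparison in all randomised, using the same Mann–Whitney test on one of these:

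- days alive and out of hospital from the procedure to day 28, with days after death counted as zero; or
- stay from the procedure, with deaths by day 28 given the worst rank.

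Either choice also sets a common starting day. Report raw length of stay descriptively by arm, beside survival.

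Cost: no added patients or visits, since survival to day 28 and hospital records are already collected. The measure is slightly less familiar. The wording change needs the approvals that the section on protocol amendments {25} requires (safety board and ethics and research governance committee). If readmission days are subtracted, they must be extracted from hospital records and the day 7 and day 28 contacts, because readmission is named only as a bleeding criterion and all-cause readmission is not a listed outcome.
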